**List of Attachments**

| Appendix 1 | Study Schedule |
| --- | --- |
| Appendix 2  Table 1 | Blood Sampling Summary  Trial Flow chart |
|  |  |
| **Appendix 1 Study schedule**  Total n=30: Obtain informed consent.  Screen potential participants by inclusion and exclusion criteria.  Physical examination, ECG, Chest X-ray and screening investigations  QoL outcomes assessment  Visit 1  Prior to  Enrolment  Entry into trial  Blood and urine samples collected for translational research  Commence ARN 509 administration  Visit 2  Week 0  Follow-up assessments for drug related side effects  Physical examination  QoL outcomes assessment  Visit 3  Week 4  Follow-up assessments  (physical examination, blood tests (FBC, renal panel, urine tests, PSA levels), urinalysis and QoL outcomes)  (blood and urine samples for translational research)  Visit 4  Week 12  Standard of care surgery  Week 12-16  Visit 5  Week 20-24 | **Final Assessments**  Physical examination  Blood tests (PSA level)  Blood and urine samples for translational research  QoL outcomes |
|  |  |

**Appendix 2 Blood sampling schedule**

| Patients on treatment arm with ARN509 | | | | | | | | |
| --- | --- | --- | --- | --- | --- | --- | --- | --- |
| Trial Period | | Screening | ARN 509 | | Follow-up (1) | Standard of care surgery | Follow-up (2) | Remarks |
| Week | | -4 | 0 | 4 | 12 | 12-16 | 20-24 |  |
|  | |  |  |  |  |  |  |  |
| **Laboratory procedures** | | | | | | | | |
| FBC with differentials | | X |  |  | x |  |  |  |
| Renal panel including calcium and phosphate levels | | x |  |  | x |  |  |  |
| Liver panel | | X |  |  | x |  |  |  |
| PSA levels | | X |  |  | x |  | x |  |
| Urinalysis | | X |  |  | x |  |  |  |
| Thyroid function test | | X |  |  |  |  |  |  |
| Hepatitis and HIV status | | X |  |  |  |  |  |  |
|  | | | | | | | | |
| Trial Period | | Screening | ARN 509 | | Follow-up (1) | Standard of care surgery | Follow-up (2) | Remarks |
| Week | | -4 | 0 | 4 | 12 | 12-16 | 20-24 |  |
| **Protocol specific collection** | | | | | | | | |
| Blood | CTCs from peripheral blood |  | x |  | x |  | x |  |
| Plasma ( ctDNA, miRNA, exosomes) |  | X |  | x |  | x |  |
| PBMC genotypic analysis |  | X |  | x |  | x |  |
| Serum (biomarkers) |  | X |  | x |  | x |  |

**Table 1. ARN 509 Phase II Investigator initiated trial Singapore General Hospital - Trial Flow Chart**

| Patients on treatment arm with ARN509 | | | | | | | |
| --- | --- | --- | --- | --- | --- | --- | --- |
| Trial Period | Screening | ARN 509 | | Follow-up (1) | Standard of care surgery | Follow-up (2) | Remarks |
| Week | -4 | 0 | 4 | 12 | 12-16 | 20-24 |  |
|  |  |  |  |  |  |  |  |
| **Administrative procedures** | | | | | | | |
| Informed consent for trial and biochemical research | X |  |  |  |  |  |  |
| Inclusion/ exclusion criteria | x |  |  |  |  |  |  |
| Subject identification card | x |  |  |  |  |  |  |
| Medical history |  |  |  |  |  |  |  |
| ECOG performance assessment | x |  |  |  |  |  |  |
| Concomitant medication review | x |  |  |  |  |  |  |
|  |  |  |  |  |  |  |  |
| **Clinic procedures** | | | | | | | |
| Full physical examination | X |  |  | X | x | x |  |
| Vital signs, Body mass index | x |  |  | X | x | x |  |
| 12 lead ECG | x |  |  |  |  |  |  |
| Chest X Ray | x |  |  |  |  |  |  |
| ARN509 administration |  | X | X | x |  |  |  |
| SOC surgery |  |  |  |  | x |  |  |
| Adverse Events monitoring |  | x | x | X | x | x |  |
| Assessment of surgical complications |  |  |  |  | x | x |  |
| Assessment of QoL outcomes (QLQC30, PR25 and SHIM) | x |  | x | x |  | x |  |
|  |  |  |  |  |  |  |  |
| **Laboratory procedures** | | | | | | | |
| FBC with differentials | X |  |  | x |  |  |  |
| Renal panel including calcium and phosphate levels | x |  |  | x |  |  |  |
| Liver panel | X |  |  | x |  |  |  |
| PSA levels | X |  |  | x |  | x |  |
| Urinalysis | X |  |  | x |  |  |  |
| Thyroid function test | X |  |  |  |  |  |  |
| Hepatitis and HIV status | X |  |  |  |  |  |  |

| Trial Period | | Screening | ARN 509 | | Follow-up (1) | Standard of care surgery | Follow-up (2) | Remarks |
| --- | --- | --- | --- | --- | --- | --- | --- | --- |
| Week | | -4 | 0 | 4 | 12 | 12-16 | 20-24 |  |
| **Protocol specific collection** | | | | | | | | |
| Blood | CTCs from peripheral blood |  | x |  | x |  | x |  |
| Plasma ( ctDNA, miRNA, exosomes) |  | X |  | x |  | x |  |
| PBMC genotypic analysis |  | X |  | x |  | x |  |
| Serum (biomarkers) |  | X |  | x |  | x |  |
| Urine | Urine (miRNA, exosomes) |  | X |  | x |  | x |  |
| Tissue | Pre-treatment prostate cancer tissue (needle biopsy)  (DNA, RNA, IHC, methylation status) |  | x |  |  |  |  |  |
| Post -treatment prostate cancer tissue (whole mount prostate tissue)  (DNA, RNA, IHC, methylation status) |  |  |  |  | x |  |  |
| FFPE benign tissue via laser capture microdissection (DNA, RNA, IHC) |  | x |  |  | x |  |  |

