| The potential direct benefits to participants include:  (i) better long term cancer control when there is synergism between neoadjuvant androgen receptor inhibition and radical surgery  (ii)  better understanding of the clinical efficacy of ARN509 in organ confined prostate cancer will potentially allow wider clinical indications for this new drug.  (iii) with better long term cancer control, there is a lower risk of recurrence and the need for future treatment including prolonged androgen deprivation therapy or radiation therapy  (iv) downstaging of disease in the prostate allows for higher probability of nerve sparing surgery which will lead to better functional outcomes of continence and potency  (v) the background information from this study may allow the study team to progress onto a multi-centre, double-blind, placebo controlled trial which will enhance the care of prostate cancer for patients  The indirect benefits to the participants include:  (i) better understanding of the biological response of human prostate cancer to ARN 509 which will potentially give insight to new therapeutic options |
|  |
| **STUDY POPULATION** |
| List The Number and Nature of Subjects to be Enrolled. |
| This will be a single centre study recruiting n=30 patients. Only male patients between 21-75 years of age will be recruited as this age range represents the surgical cohort predominant in our local practice. |
| Criteria for Recruitment and Recruitment Process |
| Suitable patients will be screened by the study team investigators and recruited in the outpatient clinics in the Singapore General Hospital. |
| Inclusion Criteria |
| The inclusion criteria include   1. those aged between 21 to 75 years of age with histologically diagnosed primary adenocarcinoma of the prostate gland within 6 months of recruitment 2. non-metastatic D’Amico intermediate to high risk patients undergoing radical prostatectomy as primary definitive therapy 3. no known hypersensitivity to the study drug 4. able to swallow study drug as whole tablets |
| Exclusion Criteria |

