| All potential subjects are referred from their primary urologists. They will be screened by a member of the study team, and the procedure will include:   1. a detailed history and clinical examination 2. screening investigations including FBC, renal panel. liver panel, thyroid function, urinalysis, PSA, hepatitis screen, chest X ray and ECG   These screening tests should be done after clinical eligibility is ascertained and the recruitment into the trial should occur within 4 weeks of screening.  In addition to the blood samples taken for screening, peripheral blood will be collected at the following occasions: (i) during trial entry, at the completion of ARN 509 therapy timed together with pre-operative blood tests, and after surgery timed together with post surgery PSA assessment About 50ml of blood will be taken at each venepuncture. A total of 175 ml for all study related blood tests is expected.  Voided urine about 150ml will be taken at the same timing as peripheral blood. A total of 470ml of urine will be expected to be collected.  These samples may be tested for the following, inclusive but not limited to proteomics, genetics and cytokines testing.  The samples will be retained at the end of the study by the investigator and stored in a secure room in SGH. Only the study team will have access to the study samples. In the event the samples are required to be transported outside SGH to a service provider, these samples will be coded.  The subject can withdraw consent to participate in the sample collection and/or for their samples to be retained at any time and still continue with the study.  Sample analysis is restricted to purposes of this study and not for future unknown usage. |
| Study Visits and Procedures |
| The following are scheduled during the intervention phase of the study:   1. week 0 where patients will receive ARN 509 2. week 4 after commencement of ARN 509 for clinical consult, physical examination and QoL outcomes 3. week 12 at completion of ARN 509 treatment, where clinical examination, blood investigations, QoL outcomes and adverse effects monitoring is performed 4. Standard of care surgery by week 16 5. Final visit at weeks 20-24 for a clinical examination, QoL outcomes, adverse effects monitoring and serum PSA assessment |
| Final Study Visit: |

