| An adverse event (AE) is any untoward medical occurrence in a patient or clinical investigation subject administered a pharmaceutical product and which does not necessarily have a causal relationship with this treatment.  A serious adverse event (SAE) or reaction is any untoward medical occurrence that at any dose:   - results in death - is life-threatening - requires inpatient hospitalisation or prolongation of existing hospitalisation - results in persistent or significant disability/incapacity or - is a congenital anomaly/birth defect - is a medical event that may jeopardize the patient and may require medical or surgical intervention to prevent one of the outcomes listed above.   Potential Discomforts, Side Effects, and Risks Associated with Apalutamide  The possible discomforts, side effects, and risks related to apalutamide treatment are not all known. Though, most side effects are not serious, some may be serious and may require treatment or additional testing. This section describes how frequently side effects occurred in subjects who were treated with apalutamide.  There may be risks with the use of apalutamide that are not yet known. You will be watched carefully during this study for any side effects. Sometimes during a study the sponsor or study doctor may learn new facts about the study medications. It is possible that this information might make you change your mind about being in the study. If new information is discovered, your study doctor will tell you about it.  Side effects may be mild or serious. All medicines have the potential to cause an allergic reaction. Some allergic reactions and side-effects may potentially be life threatening. If you do experience any side effects, your doctor may need to give you medicines to help lessen the side effect. Many side effects may go away soon after you stop taking thestudy medicine. In some cases, side effects can be serious or long lasting.  If you experience a side effect, your treating doctor may change your study drug doses in an effort to decrease or stop any side effects.If severe side effects do develop, you and your doctor may decide that it is in your best interest to stop taking part in the study. If you choose, you always have the right to withdraw from the study. In addition, you will be provided with the telephone numbers for people who can answer any questions about the study, your rights as a study participant and for you to report any side effects.  Risks and side effects that may be possibly related to apalutamide include:   | **Very Common (>10%)** | **Common (1-10%)** | **Very Rare ( < 1%)** | | --- | --- | --- | | Fatigue | Itching | Seizures | | Diarrhoea | Falls |  | | Nausea | Insomnia |  | | Vomiting | Increase in blood cholesterol |  | | Skin rash | Increase in blood triglycerides |  | | Abdominal pain |  |  | | Changes in thyroid function |  |  | | Taste alterations |  |  | | Constipation |  |  | | Decreased appetite |  |  | | Hot flashes |  |  | | Dizziness |  |  |   Seizures have been observed very rarely in patients taking part in apalutamide studies that are still blinded (blinded means that neither the doctor nor the patient knows whether the patient is receiving apalutamide or placebo). Your doctor will confirm that you have no history of seizures and will check throughout the study that you are not taking other medications that can increase your risk of seizures. Please inform your doctor of all medications you take and any changes in medications. If you think you might have had a seizure, or convulsion, or have lost consciousness (passed out), let your doctor know right away.  Some patients on apalutamide studies have developed a rash. The cause of the rash is not known. The rash may be confined to one area of your body or may involve your entire body. If you start to develop a rash on any part of your body, or if you develop any other symptoms that are worrisome to you, contact your study doctor right away.  The effect of the study drug on your semen is unknown. To avoid risk of drug exposure to your partner through the semen (even in men with vasectomies [tubes that carry semen from the testicles have been cut]), or cause harm to an unborn child, you must use a condom during sexual activity while on study drug and for 3 months following the last dose of study drug.  Apalutamide may cause harm to the unborn child. From when you start taking the study drug until 3 months after your last dose of study drug, you must use a condom and another effective method of birth control when you have sex with a woman of child-bearing potential. The type of birth control you use must be discussed with, and approved by, the study doctor before you begin the study. This is done to prevent pregnancy. If your partner becomes pregnant in the time between when you start taking the study drug until 3 months after your last dose of drug, you must tell the study doctor immediately.  Donation of sperm is not allowed during the study and for 3 months following the last dose of study drug.  You should advise your study doctor if you father a child while participating in the research project. The doctor will advise you on any appropriate medical attention for your partner should this be necessary. The sponsor may ask you and your partner to allow him/her to collect information about her pregnancy and the health of the baby. |

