| - - - 1. Safety Analyses   Drug related adverse effects will be graded according the CTCAE grading scale. All AEs reported will be graded according to scale and the prevalence calculated. |
| - - - 1. Interim Analyses   An interim analysis of outcomes will be performed when 50% accrual is completed.   - - - 1. Describe the types of statistical interim analyses, including their timing.   This will be performed when 50% accrual is completed, and will include:   1. safety outcomes analysis 2. study primary and secondary objectives as listed |
| **DIRECT ACCESS TO SOURCE DATA/DOCUMENTS** The investigator(s)/institution(s) will permit study-related monitoring, audits and/or IRB review and regulatory inspection(s), providing direct access to source data/document. **QUALITY CONTROL AND QUALITY ASSURANCE** The collected data will be compared with the source data ( patient case records). This will be cross checked by at least 2 members of the study team. The access to the data will also be maintained under lock and key and only accessible to the PI and co-PIs.  Evaluation of data quality is every 6 months.  The PI and co-investigators would perform the data and safety monitoring. **ETHICAL CONSIDERATIONS** This study will be conducted in accordance with the ethical principles that have their origin in the Declaration of Helsinki and that are consistent with the Singapore Good Clinical Practice and the applicable regulatory requirements.  This final study protocol, including the final version of the Patient Information and Informed Consent Form, must be approved in writing by the Centralised Institutional Review Board (CIRB) and regulatory approval from Health Sciences Authority (HSA), prior to enrolment of any patient into the study.  The principle investigator is responsible for informing the CIRB and HSA of any amendments to the protocol or other study-related documents, as per local requirement. |
| Informed Consent |
| The consent will be obtained after the patient is aware of his diagnosis and has consented to undergoing radical prostatectomy for prostate cancer.  Consent will be obtained by PI and co-PIs, and will be taken in the outpatient clinic. This is the most common location where patients are told of their diagnosis and counselled for surgery.  Patients will be told that their treatment and follow-up will not be influenced by their decision on enrolment into the study.  We will recruit English speaking patients. There will be no minors. |

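### Thyroid change is listed as a very common possible effect of apalutamide, but thyroid function is scheduled only at screening, so laboratory changes on treatment cannot be systematically detected

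*Protocol*

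**What the plan says.** Section 7.1 (Definitions) introduces its risk table with "Risks and side effects that may be possibly related to apalutamide include". The first column is headed "Very Common (>10" per cent, and "Changes in thyroid function" is one of its entries.

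The thyroid test appears in three places, always before treatment:

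- The screening section names it among "screening investigations including FBC, renal panel. liver panel, thyroid function, urinalysis, PSA" and other entry tests.
- Table 1 (Trial Flow Chart) has "Thyroid function test | X", with the mark under screening and nothing under weeks 0, 4, 12, surgery or 20-24.
- Appendix 2 (Blood sampling schedule) has "Thyroid function test | | X", again under screening only.

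Both tables repeat blood count, renal panel, liver panel, PSA and urinalysis at week 12. The visit description for week 12 mentions blood investigations without itemising them, and the week 12 list in Appendix 1 does not name a thyroid test.

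On analysis, section 9.2 (Safety Analyses) states: "All AEs reported will be graded according to scale and the prevalence calculated". The secondary safety objective is narrower: the rate of CTCAE events of grade 3 or above.

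**The concern.** A change in thyroid function is a laboratory finding that a patient may not feel. Section 7.4 collects adverse events by asking subjects about them, and asking cannot reveal a change without symptoms. The scheduled thyroid value has no on-treatment or post-treatment counterpart, and no inclusion or exclusion criterion uses it.

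The all-grade safety summary is at stake. The trial is meant to show that the regimen is safe and feasible and to inform a later phase III trial. A low reported prevalence of thyroid change could be read as evidence that it is uncommon, when it may only reflect that nobody measured it. No later analysis can recover a value that was not taken.

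**Working it through.** The protocol gives no figure of its own here for the number of thyroid changes, so there is none to reproduce. The check has two parts.

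**1. Schedule against risk list**

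| Test | Screening | Week 12 | Weeks 20-24 |
|---|---|---|---|
| Blood count, renal panel, liver panel, urinalysis | yes | yes | no |
| PSA | yes | yes | yes |
| Thyroid function | yes | no | no |
| Hepatitis and HIV status | yes | no | no |

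Table 1 and Appendix 2 agree on every row. Hepatitis and HIV status is the only other laboratory row that is not repeated, and it is not a listed drug effect. The Appendix 1 list for week 12 carries less weight, because it also leaves out the liver panel that both tables mark. A change from baseline needs two values per man, and the schedule supplies one.

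**2. Size, if the listed rate carries over**

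Inputs:

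- n = 30, from the study population section: "This will be a single centre study recruiting n=30 patients".
- Rate p: the risk list gives only a band above 10%. I take p = 0.10 as its lower edge. The values 0.15, 0.20 and 0.30 are an assumed range.
- All 30 men are assumed to have both a screening and a week 12 value, with independent outcomes.

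Formulas: expected count = n × p; chance of at least one = 1 − (1 − p)^30; chance of at least three = upper tail of the binomial(30, p) distribution.

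At p = 0.10 the expected count is 30 × 0.10 = 3.0, and the chance of at least one is 1 − 0.9^30 = 0.958.

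| Assumed p | Expected of 30 | At least 1 | At least 3 |
|---|---|---|---|
| 0.10 | 3.0 | 95.8% | 58.9% |
| 0.15 | 4.5 | 99.2% | 84.9% |
| 0.20 | 6.0 | 99.9% | 95.6% |
| 0.30 | 9.0 | >99.9% | 99.8% |

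Three is therefore an expected number and not a guaranteed one: at exactly 10%, three or more cases would be seen in only 59% of such trials.

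A negative result would also be informative if the test were done. With 0 changes in 30 tested men, the one-sided 95% upper limit is 1 − 0.05^(1/30) = 0.095, or 9.5%. Under the present schedule, zero reports give no such limit for laboratory changes.

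**The case against.** Several points can fairly be made against this, and some limit what may be concluded.

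- **The safety objective counts grade 3 or higher events.** This stands. The risk list gives no grade, so nothing shows that any of the expected cases would count towards that objective. A reader might infer that the trial's safety endpoint cannot detect the effect. The protocol supports this only for the all-grade prevalence in section 9.2, and there only for changes found by laboratory test.
- **Other routes to detection exist.** This stands. Table 1 has adverse event monitoring at weeks 0, 4 and 12, at surgery and at weeks 20-24. Patients are told to report suspected effects promptly, and week 12 includes an examination. A symptomatic change, or one found on an unscheduled test, can be recorded. A reader might infer that the reported prevalence will be close to zero by design, but the documents do not say what share of thyroid changes is without symptoms.
- **The rate is not an assumption of this trial.** This stands. The list is patient-directed text about possibly related effects in treated subjects, with no treatment duration or method of ascertainment. It would go too far to say that the protocol expects three cases.
- **A risk list is not a measurement plan.** This stands in part. Raised cholesterol and triglycerides are also listed and never scheduled, and no text promises thyroid testing on treatment. But those effects are in the 1-10% band, whereas thyroid change is in the highest band, already has a baseline test, and could use a planned week 12 draw. The screening value could serve as a reference if symptoms prompted a test, but that would not be systematic.
- **A week 12 test would not by itself enter cases into the adverse event counts.** This stands, because section 7.1 gives no rule for when an abnormal value without symptoms is an adverse event. The fix therefore needs a reporting element.

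**Conclusion.** The point holds in a limited form. The protocol ranks thyroid change in its most frequent band of possible effects but schedules no thyroid test on or after treatment, so scheduled data cannot systematically detect laboratory changes. The all-grade prevalence may be understated by an amount the documents do not allow one to calculate, because the share without symptoms is not given.

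If the listed rate applies to a 12-week course, the number of men with any thyroid change would be expected to be 3 or more of 30, with a 96% chance of at least one at 10%. That transfer is an assumption. The primary objectives are untouched and the grade 3 or higher objective is not shown to be affected. A reader might also infer a consequence for men going on to surgery, but the documents contain nothing to support one. This is an inexpensive improvement to the safety evidence and not a fault in the main result.

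**What to change.** Reconcile the laboratory schedule with the risk list:

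1. Mark the thyroid function test at week 12 in Table 1 and Appendix 2, as an outcome measurement on the blood draw already planned, and name it in the week 12 list in Appendix 1.
2. In section 9.2, state that change from the screening value will be reported alongside the CTCAE results, with the number of men tested as the denominator. The finding is then captured whether or not it is recorded as an adverse event.

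The cost is one extra assay per man, about 30 in all, plus the table entries and one sentence of analysis text. No new visit or venepuncture is needed. The change concerns measurement and reporting only and implies no treatment action.
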